#### Dietary supplements

All study participants will follow the supplement regimen outlined in Table 1, with the exception of vitamin D_3_ (amount prescribed will vary on the basis of vitamin D level measured in the blood at visit 1 and subsequent visits as outlined in Table 2; target range, 40–80 ng/ml). After review of participant’s dietary supplement intake, study staff will ask participants to discontinue over-the-counter dietary supplements containing the study supplement ingredients (fish oil, vitamin D, vitamin B_12_, folate, and/or multivitamins) and use study supplements instead. Participants will be instructed to continue taking all other dietary supplements they have been using and not to begin any new supplements until after study completion. If the participant is asked to discontinue a supplement recommended by their physician or neurologist, the research team will send a letter to the treating physician, detailing which supplements have been discontinued and which supplements have been initiated as part of the study protocol.

**Table 2 Tab2:** Vitamin D dosing based on blood level

If vitamin D > 100 ng/ml and elevated calcium (Ca^2+^) > 10.2 mg/dl • Call study participant and have them stop vitamin D immediately, increase water intake. a. If Ca^2+^ level was 10.2–10.5: call your local physician, or urgent care for guidance. b. If Ca^2+^ level was 10.6 or higher: go to the emergency room for evaluation and probable intravenous fluids. • Stop or do not start taking the cod liver oil or the multivitamin • When vitamin D < 80 ng/ml, resume vitamin D at a reduced dose and cod liver oil and multivitamin per local primary care or neurology guidance • Call and notify the study participant’s primary care/neurology team about the high vitamin D level • Send letter to participant and primary care/neurologist	
If vitamin D > 100 ng/ml and normal calcium Ca^2+^ 8.5–10.2 mg/dl • Study staff will call the participant and have them stop all vitamin D supplements. Participant will follow up with their primary care doctor or neurologist. • Stop or do not start taking cod liver oil but may continue multivitamin • When vitamin D < 80 ng/ml, may resume vitamin D at a reduced dose and cod liver oil and multivitamin per local primary care or neurology guidance • Call and notify the study participant’s primary care/neurology team about the high vitamin D level • Send letter to participant and primary care/neurologist	
If vitamin D between 81 and 100 ng/ml • Start or continue taking cod liver oil and multivitamin • Reduce total vitamin D intake by 50% ∘ The goal is half the dosage from all sources participant was taking at the time the blood measurement was made ∘ If the vitamin D_3_ supplement dosage was in fractions; then, round it down to the next available pill in the market. ∘ E.g., if the total taken is 7000; 1000 from MV, 1000 from calcium/vitamin D_3_ supplement and 5000 IU vitamin D_3_ we want to halve the dose; then the total amount to take becomes 3500. We will ask the participant to continue calcium/vitamin D_3_ (1000 IU), switch to our MV (1000 IU), start cod liver oil (400 IU), which totals 2400. The remaining vitamin D_3_ (3500–2400) is 1100 IU (round down to 1000 IU), so we prescribe a 1000-IU pill once daily. • Send letter to participant and primary care/neurologist	
If vitamin D 40 to 80 ng/ml At visits 2, 3, and 4: • Start or continue taking cod liver oil and multivitamin which contain about 1400 IU between the two supplements. Keep participant on current dose of vitamin D if in this range. At all visits: • Do not change vitamin D dose. E.g., if the participant is taking 4000 IU from their personal physician, participant should stay on that dose. If they were taking 5000 IU from their personal physician they should stay on that dose. If participant is taking more than 5000 IU or less than 4000 IU, participant should continue on that dose. • No need to start vitamin D_3_ supplement if not on any.	
If vitamin D value less than 40 ng/ml but more than 20 ng/ml If visit 1 blood result: • Wait until visit 2. At visit 2: • If not taking any vitamin D, begin 5000 IU daily. Participant will also begin or continue taking cod liver oil and multivitamin according to the supplement schedule. • If taking 4000 IU vitamin D_3_ or less daily, participant will be instructed to increase vitamin D_3_ to 5000 IU and add or continue taking cod liver and multivitamin according to the supplement schedule. • If the participant is already taking 5000 IU but does not take the supplement regularly (i.e., daily) they will be instructed to take the supplement every day and add or continue taking cod liver oil and multivitamin. • If taking 5000 IU or more they should add or continue taking cod liver oil and multivitamin. Discuss with [name] for further guidance on the appropriate vitamin D dose.^a^ The patient and primary care/neurology team will be notified by letter of the lab results and the vitamin D, cod liver oil and multivitamin recommendations. • Send letter to participant and primary care/neurologist if participant is instructed to change vitamin D intake prescribed by medical personnel If visit 2 blood result: • Wait until visit 3 blood result. If visit 3 or 4 blood result: • And participant is taking 5000 IU vitamin D, cod liver oil and the multivitamin, discuss with [name] for further guidance.^a^ An increase in the vitamin D dose will likely be recommended by [name] and personalized results letters will be sent separately to the participant and their primary care/neurology team.	
If vitamin D value 20 ng/ ml or less If visit 1 or 2 blood result: • Refer participant back to primary care physician and neurologist, recommending the primary care physician or neurologist prescribe vitamin D_2_ 50,000 IU once per week until vitamin D level is greater than 40 ng/ml. Alternatively, the primary care physician may recommend 6000 to 10,000 IU vitamin D_3_ daily if preferred over vitamin D_2_. • Send letter to participant and primary care/neurologist • Call and notify participant that vitamin D level is severely low and advise them that a letter is being sent to them and their primary care/neurology team. *If visit 2, 3, or 4* • Call participant to clarify if the participant is taking any vitamin D supplements, cod liver oil or multivitamin and discuss with [name] for further guidance. If already on vitamin D_3_ 5000 IU or a vitamin D_2_ supplement per their local medical team, the participant may continue the vitamin D until they see their primary care/neurology team for further guidance. Continue or add cod liver oil and multivitamin as scheduled. • Send letter to participant and primary care/neurologist	

^a^The total vitamin D_3_ from vitamin D_3_ supplement (including cod liver oil and the multivitamin) recommended by the study team should not exceed 7000 IU/d (cod liver oil and multivitamin have approximately 1400 IU daily combined) unless approved specifically by [name].

Abbreviation: *MV* Multivitamin

**Table 3 Tab3:** Outcomes: change after 12-week intervention and 12 weeks of sustained intervention relative to observation period

Primary outcome measure:	
1. Perceived fatigue assessed by FSS.	
Secondary outcome measures:	
1. Perceived fatigue assessed by MFIS;	
2. Perceived fatigue assessed by FSMCF;	
3. Gait speed assessed by T25FW;	
4. Distance walked assessed by 6MWT;	
5. Speed of task completion in 9HPT;	
6. Number of correct responses assessed by SDMT-O;	
7. Quality of life as measured by MSQOL-54;	
8. Quality of life as measured by SF-36;	
9. MSISv2 score;	
10. Anxiety and depression as measured by HADS;	
11. Physical activity (average daily steps and average minutes spent sedentary, light intensity physical activity, moderate intensity physical activity and vigorous intensity physical activity) and sleep (total sleep time, sleep efficiency) as measured by the accelerometer;	
12. Sleep quality as measured by PSQI;	
13. Stress as measured by PSS-10;	
14. Physical activity as assessed by IPAQ-L;	
15. Cognitive performance as measured by PDQ;	
16. Change in mood as measured by the MHI.	
17. Nutritional adequacy of the diet as measured by food frequency questionnaire (FFQ) and food records;	
18. Changes in blood biomarkers (insulin, glucose, hemoglobin A1c, lipids including HDL, vitamin K, vitamin D, calcium, vitamin B_12_, folate, homocysteine, complete blood count with differential, Cardio IQ® [fatty acid levels]).	

*Abbreviations: 6MWT* 6-Minute walk test, *9HPT* 9-hole Pegboard Test, *Cardio IQ®* Omega-3 (EPA + DHA) Index, Omega-6/Omega-3 Ratio, EPA/Arachidonic Acid Ratio, Arachidonic Acid, EPA, and DHA, *DHA* Docosahexaenoic acid, *EPA* Eicosapentaenoic acid, *FFQ* Food Frequency Questionnaire, *FSMCF* Fatigue Scale for Motor and Cognitive Function, *FSS* Fatigue Severity Scale, *HADS* Hospital Anxiety and Depression Scale, *HDL* High Density Lipoprotein, *IPAQ-L* International Physical Activity Questionnaire–Long, *MFIS* Modified Fatigue Impact Scale, *MHI* Mental Health Inventory, *MSIS v2* Multiple Sclerosis Impact Scale version 2, *MSQ* Medical Symptoms Questionnaire, *MSQOL54* Multiple Sclerosis Quality of Life 54, *PDQ* Perceived Deficits Questionnaire, *PSQI* Pittsburgh Sleep Quality Index, *PSS 10* Perceived Stress Scale 10, *SDMT-O* Symbol Digit Modalities Test-Oral, *SF-36* 36-item Short Form Health Survey, *SPMSQ* Short Portable Mental Status Questionnaire, *T25FW* Timed 25-foot Walk

Study staff will provide participants with a list of supplements to purchase and will reimburse participants for all study supplements. Participants will be instructed to begin supplements on the 11th day of the diet to allow them time to purchase the supplements after returning home from visit 2. They will introduce one new supplement every third day to allow time to identify any potential adverse reactions. If side effects are noted, the participant will be told to stop the supplement and contact study staff.

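### Table 2 lets calcium hold back supplements only when vitamin D is above 100 ng/ml; the gap matters mainly in the > 20 to < 40 and 40–80 ng/ml rows

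*Protocol article*

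**What the plan says.** Dietary supplements states that the vitamin D3 amount depends on the blood vitamin D level, with a target of 40–80 ng/ml. Table 2 gives the instructions in six rows.

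- **Above 100 ng/ml.** Two rows, split by calcium: "If vitamin D > 100 ng/ml and elevated calcium (Ca^2+^) > 10.2 mg/dl" and "If vitamin D > 100 ng/ml and normal calcium Ca^2+^ 8.5–10.2 mg/dl". Vitamin D and cod liver oil are stopped in both. The multivitamin may continue if calcium is normal and is stopped or withheld if calcium is elevated.
- **81–100 ng/ml.** Cod liver oil and multivitamin are started or continued, total vitamin D intake is halved, and letters are sent.
- **40–80 ng/ml.** At visits 2 to 4: "Start or continue taking cod liver oil and multivitamin which contain about 1400 IU between the two supplements". The current vitamin D dose is kept. The row contains no letter.
- **> 20 to < 40 ng/ml.** A visit 1 result is acted on at visit 2: "If not taking any vitamin D, begin 5000 IU daily", or, for someone on 4000 IU or less, the "participant will be instructed to increase vitamin D_3_ to 5000 IU and add or continue taking cod liver and multivitamin".
- **20 ng/ml or less.** The treating physician is advised to "prescribe vitamin D_2_ 50,000 IU once per week until vitamin D level is greater than 40 ng/ml" or to use daily vitamin D3 instead. Cod liver oil and multivitamin are continued or added.

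A footnote caps the total vitamin D3 "recommended by the study team should not exceed 7000 IU/d" unless specifically approved. The Measures section lists calcium and vitamin D in one blood panel collected at each visit.

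**The concern.** Table 2 treats calcium as decisive in one place and ignores it elsewhere. Between the two rows above 100 ng/ml, calcium alone changes the multivitamin instruction from permitted to withheld. Below 100 ng/ml the same products are started, kept or raised whatever the calcium.

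The stake is participant safety. Staff who follow the printed rule could start or raise vitamin D products in someone whose measured calcium is already above the level that the table labels elevated. Visits 2, 3 and 4 fall at weeks 12, 24 and 36, so the next scheduled blood result comes about 12 weeks later. Both arms follow the same supplement regimen, so this is not a point about bias.

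**Working it through.** No power or error-rate figure is involved. The check is a row-by-row reading of Table 2, followed by the dose arithmetic.

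**1. Where calcium enters.**

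| Vitamin D (ng/ml) | Calcium condition | Action on vitamin D products | Mitigation in the row |
|---|---|---|---|
| > 100, calcium > 10.2 mg/dl | yes | all stopped or withheld | call, letter |
| > 100, calcium 8.5–10.2 mg/dl | yes | vitamin D and cod liver oil stopped | call, letter |
| 81–100 | none | cod liver oil and multivitamin started or continued; total halved | letters |
| 40–80 | none | cod liver oil and multivitamin started or continued; dose kept | none |
| > 20 to < 40 | none | vitamin D3 started at or raised to 5000 IU; other two added or continued | letters in some branches; advice sought at 5000 IU or more |
| ≤ 20 | none | repletion recommended; other two continued or added | treating physician decides; letter and call |

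Calcium appears in 2 of 6 rows.

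**2. Row > 20 to < 40.** Inputs from Table 2: 5000 IU of vitamin D3, about 1400 IU from cod liver oil plus multivitamin, and the 7000 IU/day cap.

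- Total: 5000 + 1400 = 6400 IU/day.
- Distance below the cap: 7000 − 6400 = 600 IU/day, so the cap does not bind.
- For someone on no vitamin D, the whole 6400 is new. For someone on 4000 IU and neither other product, the increase is (5000 − 4000) + 1400 = 2400 IU/day. It is smaller where study products replace the participant's own, as Dietary supplements requires.

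A visit 2 vitamin D result in this band is left until visit 3. The row therefore gives the visit 2 calcium no part in the decision, although supplements begin only on day 11 of the diet.

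**3. Row 40–80.** About 1400 IU/day is started or continued. A participant on no vitamin D3 supplement does not start one. With a kept dose of up to 7000 − 1400 = 5600 IU/day, the total stays within 7000 IU/day.

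**4. The other two rows.** In the table's own example for 81–100, intake falls from 7000 to 1000 + 1000 + 400 + 1000 = 3400 IU/day. At 20 or below, the repletion dose is the physician's decision. The gap is small in both.

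**5. The laboratory trigger elsewhere.** Risks and safety monitoring has the DSMB review values more than 10% outside the reference range. The document does not fix the range for this purpose. Assuming Table 2's 8.5–10.2 mg/dl:

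- 10% above the upper limit: 10.2 × 1.10 = 11.22 mg/dl.
- 10% of the range width: 10.2 + 0.10 × (10.2 − 8.5) = 10.37 mg/dl.

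On either reading this is board review supported by quarterly reports. It is not a dosing instruction.

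**The case against.** The strongest reply is that nothing is contradicted. The table's title and text tie dosing to vitamin D, and 10.2 mg/dl appears only jointly with vitamin D above 100 ng/ml, where calcium grades the urgency of a high vitamin D result. Handling of an isolated high calcium may sit in a general laboratory procedure that an article would leave out. There are also other safeguards: the cap, exclusion of people with kidney stones, one new supplement every third day with instructions to stop if side effects occur, a side effects questionnaire, two physicians who receive all adverse event sheets, and stopping guidelines.

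Part of this stands. The table never states 10.2 mg/dl as a free-standing limit, and a procedure outside the article is possible. The safeguards bound the exposure, but none ties a dose to calcium. The table is printed in full with detailed instructions, so the point concerns a stated rule and not something lost in condensing.

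A reader might infer more than the text supports:

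- *That all four lower rows are equally at fault.* They are not: one halves intake and sends letters, and one leaves repletion to the treating physician.
- *That a calcium of 10.6 mg/dl or more should mean the emergency room at any vitamin D level.* The table says so only above 100 ng/ml.
- *That high calcium would go unnoticed.* The > 20 to < 40 row does provide for a letter with laboratory results, although the printed layout leaves unclear whether it covers people newly starting 5000 IU. An alert may also exist elsewhere.

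**Conclusion.** The point holds for two rows. At > 20 to < 40 ng/ml, up to 6400 IU/day is directed with no calcium condition. At 40–80 ng/ml, about 1400 IU/day is started or continued on top of a kept dose, with no letter in the row. In both, the rule as printed proceeds when measured calcium exceeds the value that the table calls elevated. The remaining two lower rows are largely mitigated.

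This is a worthwhile safety correction, not a threat to the trial's conclusions. How many participants have calcium above 10.2 mg/dl in these bands is unknown and may be few. The conclusion assumes that staff act on Table 2 as printed; a general calcium alert in the full protocol would reduce its practical weight.

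**What to change.** Add one line to Table 2: *At any vitamin D level, if the latest available calcium is > 10.2 mg/dl, do not start or increase vitamin D, cod liver oil or multivitamin; notify the participant and the primary care/neurology team, who advise whether current supplements continue.* Leave the stricter instructions above 100 ng/ml unchanged.

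Before supplements begin on day 11, use the visit 2 calcium if it is back. That allows 10 days, and the turnaround time is an assumption.

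The treating team is the right route. The person whom Table 2 names for dose advice is redacted, and so is the person whom Study setting bars from participants and raw data; whether they are the same cannot be told. The line also gives no new task to the blinded medical monitor.

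The cost is a few extra notifications, occasional delayed supplementation, and a minor protocol amendment while recruitment is under way (58 consented at publication). No new blood test is needed.

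### For a participant who falls from above 100 into 81–100 ng/ml, Table 2 gives opposite instructions on cod liver oil and, only after elevated calcium, on the multivitamin

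*Protocol article*

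**What the plan says.** All references are to the protocol article, Dietary supplements, Table 2, unless stated otherwise.

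- The text that introduces the table says that the vitamin D3 amount will "vary on the basis of vitamin D level measured in the blood at visit 1 and subsequent visits as outlined in Table 2". The Measures section lists vitamin D among the blood markers collected at every visit.
- Above 100 ng/ml with elevated calcium: "Stop or do not start taking the cod liver oil or the multivitamin". The way back is "When vitamin D < 80 ng/ml, resume vitamin D at a reduced dose and cod liver oil and multivitamin", subject to guidance from the local primary care or neurology team.
- Above 100 ng/ml with normal calcium: all vitamin D supplements stop, and for the other two products "Stop or do not start taking cod liver oil but may continue multivitamin". The way back is "When vitamin D < 80 ng/ml, may resume vitamin D at a reduced dose and cod liver oil and multivitamin", again under local guidance.
- Both of these rows have staff call and notify the participant's "primary care/neurology team about the high vitamin D level", and a letter follows.
- 81 to 100 ng/ml: "If vitamin D between 81 and 100 ng/ml • Start or continue taking cod liver oil and multivitamin". The same row then says "Reduce total vitamin D intake by 50" per cent, counted from all sources at the time of the blood measurement. A worked example follows, and a letter goes to the participant and the treating team.

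**The concern.** Each row is selected by the current level, but the two rows above 100 ng/ml also contain a condition that reaches forward to later measurements: stay off until below 80. The 81–100 row lies between those two thresholds and has no exception for someone who is still off. A participant stopped at more than 100 ng/ml who next measures in that band therefore meets two printed instructions that cannot both be followed.

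The sequence is foreseeable. A high vitamin D level is not an exclusion criterion, stopping supplements is meant to bring the level down, and a level falling from above 100 to below 80 passes through this band. Staff who read only the row for the current level would put the participant back on products that were withheld on safety grounds. They would also do so without the local medical decision on which the higher rows make resumption depend.

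**Working it through.** **The rows side by side, for a participant above 100 ng/ml at one visit and at 90 ng/ml at the next**

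| Blood result at the previous visit | Row above 100, still in force because 90 is not below 80 | 81–100 row at 90 ng/ml | Conflict |
|---|---|---|---|
| Above 100, elevated calcium | Cod liver oil off, multivitamin off | Both on | Both products |
| Above 100, normal calcium | Cod liver oil off, multivitamin allowed | Both on | Cod liver oil only |
| Never above 100 | Does not apply | Both on | None |

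**Inputs.** The 81–100 row's example gives 1000 IU for the study multivitamin and 400 IU for cod liver oil. The sum, 1000 + 400 = 1400 IU/day, agrees with the combined figure in the 40–80 row and in the table's footnote. The standard study vitamin D3 dose in Table 1 is 5000 IU.

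**The table's own example reproduces.** Intake is 1000 + 1000 + 5000 = 7000 IU, and half is 3500. Kept or started: 1000 (calcium/vitamin D product) + 1000 (multivitamin) + 400 (cod liver oil) = 2400. The remainder is 3500 − 2400 = 1100, rounded down to a 1000 IU pill. The total is 3400 IU, a cut of (7000 − 3400)/7000 = 51%.

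**Size of the conflict.** This assumes no vitamin D source beyond the two products, and the study multivitamin's content.

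- After normal calcium with the multivitamin continued, intake goes from 1000 to 1400, so 400 IU/day is in dispute. That is 400/5000 = 8% of the standard D3 dose. The row's halving goal would be 500.
- After elevated calcium with both stopped, intake goes from 0 to 1400, so 1400 IU/day is in dispute, or 1400/5000 = 28% of the standard dose. The halving goal would be 0.

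In both cases, following the 81–100 row raises intake although the row exists to lower it.

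**A separate limit of the same row, for any participant.** Let T be intake at measurement in IU/day. The goal is T/2, and taking both products gives at least 1400. The goal can be met only if T/2 ≥ 1400, that is T ≥ 2800. Intake rises whenever T < 1400.

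| T | Goal T/2 | Lowest total with both products | Change from T |
|---|---|---|---|
| 0 | 0 | 1400 | starts from none |
| 1000 | 500 | 1400 | +40% |
| 1400 | 700 | 1400 | 0% |
| 2000 | 1000 | 1400 | −30% |
| 2800 | 1400 | 1400 | −50% |

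**When it can occur.** Two measurements are needed, so the earliest is visit 2 (week 12). Visits 2 and 3 are each followed by a 12-week study period. Visit 4 (week 36) is the last scheduled visit.

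**The case against.** The best reply is that the condition on resuming below 80 can operate only at a later, lower measurement. If the 81–100 row overrode it, the condition would have no effect anywhere in that band. Reading the specific condition as governing the general row gives every line some effect. The 81–100 row also looks written for someone currently taking vitamin D: it halves a current intake, and its example is a 7000 IU user. This reading is plausible and probably what was intended. What stands against it is that the table never says so, although it writes its conditions out elsewhere: the 40–80 row ties an instruction to visits 2, 3 and 4, and the 20–40 row says to wait after a visit 2 result. The 81–100 row is limited neither by visit nor by earlier level, and it covers starting as well as continuing.

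It can also be said that a journal article leaves operating detail to the full protocol. Table 2, however, is printed down to pill rounding, and the point is that two printed instructions conflict, not that something is absent.

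The safeguards are real. The treating team is called and sent a letter after a level above 100, a letter goes out in the 81–100 band, and the safety board reviews laboratory values that are well out of range.

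Three stronger readings are tempting and not supported:

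- A reader might infer that both rows above 100 withhold the multivitamin, because both list it among the items to resume. The normal-calcium row expressly lets it continue, so the multivitamin conflict needs elevated calcium.
- A reader might count visit 4 as well. No study period follows it.
- A reader might expect bias in the diet comparison. Both arms share the supplement regimen, and nothing in the documents points to an effect on the fatigue results.

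**Conclusion.** The point holds as a minor inconsistency in a safety rule. For a participant once above 100 ng/ml whose next level is 81–100 ng/ml, Table 2 conflicts on cod liver oil (about 400 IU/day) and, only if calcium had been elevated, on cod liver oil and multivitamin together (about 1400 IU/day). These amounts assume no other vitamin D source and the product contents given in the table. The consequences within the study arise at visits 2 and 3. The documents do not say how many participants would follow this path; it is probably few. For participants never above 100 ng/ml these rows do not conflict.

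The 2800 IU/day threshold is a distinct problem. It applies to anyone with a low intake in the 81–100 band, whatever their earlier level, and resolving the conflict does not resolve it.

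**What to change.** In the 81–100 row, keep the first instruction and add an exception: any product stopped or not started because of an earlier level above 100 ng/ml stays off until the level is below 80 ng/ml, and is then resumed under the guidance of the local primary care or neurology team. The reference to local guidance should be kept, because both higher rows make resumption depend on it.

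For the separate limit, add to the same row that a product is not to be started if doing so would take total vitamin D intake above the halved goal. This prevents the rise. It does not by itself produce a 50% cut for someone whose whole intake already comes from the two products (T = 1400, goal 700), and the sponsor may wish to say what is acceptable there.

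The cost is two short clauses in one row of Table 2, with the usual notification to the ethics board. Data collection, sample size and the efficacy analysis do not change.

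### Table 2, 81–100 ng/ml row: keeping cod liver oil and multivitamin (about 1400 IU/day) and halving all vitamin D cannot both be done below a prior intake of about 2800 IU/day (minor)

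*Protocol article*

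**What the plan says.** The section Dietary supplements sets a target range of 40–80 ng/ml and one regimen for both diets, with vitamin D3 as the adjustable part: "All study participants will follow the supplement regimen outlined in Table 1, with the exception of vitamin D_3". Table 2 gives the dosing rules by blood level.

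- The 81–100 ng/ml row instructs: "Start or continue taking cod liver oil and multivitamin • Reduce total vitamin D intake by 50" per cent. It defines the base for the cut: "The goal is half the dosage from all sources participant was taking at the time the blood measurement was made".
- Its example starts from 7000 IU/day. The participant is to "continue calcium/vitamin D_3_ (1000 IU), switch to our MV (1000 IU), start cod liver oil (400 IU), which totals 2400", and the remainder up to half the prior total is filled with a D3 pill, rounded down. It ends: "so we prescribe a 1000-IU pill once daily. • Send letter to participant and primary care/neurologist".
- The 40–80 ng/ml row gives the content of the two products: "cod liver oil and multivitamin which contain about 1400 IU between the two supplements". The table footnote repeats this figure. The same row adds: "No need to start vitamin D_3_ supplement if not on any". A participant can therefore be on the two products and nothing else.
- On timing: "Participants will be instructed to begin supplements on the 11th day of the diet". The diet begins after visit 2, so results from visits 1 and 2 reflect intake before the study products.

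Neighbouring rows have a way out that this row lacks. Both rows above 100 ng/ml withhold cod liver oil, and one also withholds the multivitamin. The rows below 40 ng/ml include a step to ask a named member of the study team for guidance.

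**The concern.** The row gives two instructions without conditions. One fixes a minimum intake of about 1400 IU/day from the two products. The other fixes a maximum of half the prior intake. When half the prior intake is below the minimum, no dose satisfies both. The only example uses a prior intake high enough to hide this.

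At stake is whether a dose-reduction rule, for participants already above the trial's own target, reduces the dose. At low prior intake it can leave the dose unchanged or raise it.

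**Working it through.** **Inputs.** Study multivitamin 1000 IU and cod liver oil 400 IU (example in the 81–100 row); together about 1400 IU (40–80 row and footnote). Let T be the prior intake from all sources and K the vitamin D in any other product that is kept.

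**The row's own example.** T = 1000 + 1000 + 5000 = 7000. Half is 3500. Products taken: 1000 + 1000 + 400 = 2400. Remainder 3500 − 2400 = 1100, rounded down to 1000. New total 2400 + 1000 = 3400 IU/day. The example is correct.

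**General condition.** D3 pill = T/2 − (1400 + K). This cannot be negative, so both instructions hold only if T ≥ 2 × (1400 + K).

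- K = 0: T ≥ 2800 IU/day.
- K = 1000, the kept product in the example: T ≥ 2 × 2400 = 4800 IU/day.
- The content is stated as approximate. If the true figure were 1300 to 1500 IU (assumed range), the K = 0 threshold would be 2600 to 3000 IU/day.

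**Best result below the threshold**, with K = 0, both products taken and no D3 pill. Change = 1400/T − 1.

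| Prior T (IU/day) | Goal T/2 | Lowest total | Above goal | Change from T |
|---|---|---|---|---|
| 2800 | 1400 | 1400 | 0 | −50% |
| 2400 | 1200 | 1400 | 200 | −42% |
| 2000 | 1000 | 1400 | 400 | −30% |
| 1400 | 700 | 1400 | 700 | 0% |
| 1000 | 500 | 1400 | 900 | +40% |

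**Which rows of the table can arise.**

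- T = 1400: a participant in the 40–80 range at visit 2 who takes no D3 pill starts the two products alone. If visit 3 then reads 81–100, the row yields no reduction. In practice this concerns visit 3, because visit 4 is the last visit.
- T below 1400: essentially limited to results from visits 1 and 2, since the products start after visit 2. From then on a participant following the regimen already takes about 1400 IU/day, so the row can fail to reduce intake but does not raise it.

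**The case against.** The strongest reply is that staff do have a procedure. The regimen is common to everyone except for D3, and the example subtracts the products first and fills only what remains. When nothing remains, no pill is given. The halving is also worded as a goal. This much stands: a reader might infer that the row leaves staff not knowing what to do about D3, and the text does not support that. What remains is that the stated 50% is missed even on this reading. Calling it a goal does not explain a reduction step that changes nothing or adds vitamin D.

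A second reply is that the failing cases need a level above 80 ng/ml on less than about 2800 IU/day, and nothing in the article shows that this happens. That also stands. The cases can be reached by following the table, but the article gives no frequency.

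Third, the excess over the goal is 200 to 900 IU/day in the cases tabulated, against a Table 1 D3 dose of 5000 IU and a footnote cap of 7000 IU/day. Vitamin D and calcium are measured at each visit, the treating physician receives a letter, the safety board reviews laboratory values more than 10% outside the reference range, and both rows above 100 ng/ml stop vitamin D. These points limit the size of the problem but do not remove the conflict.

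Finally, rare cases may be handled in the full protocol. But the point is not that detail is missing: two instructions printed in the same row of a detailed dosing table conflict.

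**Conclusion.** The defect is real and minor, and correcting it is optional. Below a prior intake of about 2800 IU/day (about 4800 if a 1000 IU product is kept) the 81–100 ng/ml row cannot deliver its own 50% reduction. It delivers none at 1400 IU/day, and it raises intake for a participant with a visit 1 or 2 result who was taking less than that.

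The figures rest on the stated content of about 1400 IU, on both products being taken as instructed, and on no D3 pill being given when nothing remains. How many participants would be affected is unknown and probably small.

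Two stronger conclusions might be inferred, and neither is supported. The first is that the dosing arithmetic is wrong: the worked example is right, and only the rule's reach is too wide. The second is that the trial's results are threatened: the regimen and the rule are the same for both diets, so power and the between-group comparison are unaffected.

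**What to change.** Add one line to the 81–100 ng/ml row: if half the prior total is below the vitamin D content of the products to be taken, give no D3 pill, do not start a product that would raise total intake above the prior level, and refer to the study's medical lead on whether to hold cod liver oil or multivitamin. Record any withholding, because fatty acid levels are an outcome (Table 3, item 18).

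Some arithmetic may help the medical lead. With no other source kept, holding cod liver oil leaves 1000 IU, which meets the goal when T ≥ 2 × 1000 = 2000. Holding the multivitamin instead leaves 400 IU, which meets it when T ≥ 2 × 400 = 800.

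The cost is one line in one table row, a note to staff, a few extra consultations, and rare recorded deviations from the common regimen. At publication 58 participants had consented, against a planned 2 × 45 = 90, so the change could still have applied to later participants.
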